1  
2  
3  
4  
5  
6  
7  
8  
9  
10  
11  
12  
13  
14  
15  
16  
17  
18  
19  
20  
21  
22  
23  
24  
25  
26  
27  
28  
29

| Protocol version | Date of Issue | Summary of changes                                                                                                                                                                                                                                                                                                                                                                                                                                                                                                              |
|------------------|---------------|---------------------------------------------------------------------------------------------------------------------------------------------------------------------------------------------------------------------------------------------------------------------------------------------------------------------------------------------------------------------------------------------------------------------------------------------------------------------------------------------------------------------------------|
| 1                | 2022-01-10    | Included the questionnaire Perth Alexithymia Questionnaire (PAQ) to measure Alexithymia.
Included assessments three-month post-treatment.
Expanded the numbers of exclusion criteria before study commenced.                                                                                                                                                                                                                                                                                                              |
| 2                | 2023-08-30    | Decided not to analyze and report for main outcome paper: 

- Weekly measures of Revised Child Anxiety and Depression Scale and the Cognitive Emotion Regulation Questionnaire.

- Strengths and Difficulties Questionnaire.

- Brief 16-item Version of the Difficulties in Emotion Regulation.

- Emotion Regulation Questionnaire Child/Adolescents Version.

- Beliefs About Emotions Questionnaire

- Emotion Regulation Diversity Index.

 |
| 3                | 2025-03-2     | Statistical analysis was updated in response to reviewers' comments and the decision to remove all between group analysis and only present within group analysis separately for the two intervention groups.                                                                                                                                                                                                                                                                                                                    |

86  
87    Contact information

| Responsibility in the clinical trial |                                                                                                                                              |
|--------------------------------------|----------------------------------------------------------------------------------------------------------------------------------------------|
| Sponsor representative               | [name], Licensed medical doctor
Gustavsbergs vårdcentral
[name],
Sweden                        |
| Principal Investigators              | [name], Associate professor
Karolinska institutet
[name]
[name]
[contact] |

## Background

Mental health problems in youth are a global problem, causing incalculable suffering in youth and families, harming long-term prospects of youths, and creating substantial economic costs to society. Although treatments exist, these treatments are not fully addressing these problems for several reasons. First, although many youth in need of treatment for mental health problems do not meet criteria for any mental health disorder or they meet criteria for several disorders, most treatments focus on a subset of mental disorders and do not address subthreshold or multi-disorder mental health problems. Second, available treatments do not typically target transdiagnostic disease mechanisms. Third, the available treatments are limited in efficacy. Fourth, most youth in need do not receive treatment due to social stigma and structural barriers such as geographical distance to treatment providers. Of particular concern is the lack of attention to subthreshold or multi-disorder mental health problems. There is a lack of evidence-based treatment protocols for patients without a formal disorder or fulfilling criteria for several disorders – a problem that has recently been identified within Swedish primary mental health care. Many leading researchers and institutions have suggested that progress within mental health research and treatment requires a shift away from a focus on specific mental disorders to a more transdiagnostic perspective, addressing underlying processes. One promising observation in this direction is the robust finding that the frequency of usage of adaptive and maladaptive emotion regulation strategies is related to a wide range of mental health problems, suggesting that emotion regulation may be an important treatment target. Indeed, a meta-analysis indicates that interventions targeting emotion regulation in youth can improve mental health problems. However, the authors highlight that there is limited evidence with respect to interventions targeting emotion regulation in different age groups and psychopathologies, as well as a lack of longitudinal studies investigating the temporal relationship between emotion regulation and psychopathology. The authors conclude that appropriately sized randomized controlled trials (RCT) evaluating scalable transdiagnostic treatments targeting emotion regulation are urgently needed to assess both how well they work in youth (i.e., improve mental health) and the mechanisms by which they work (e.g., through improved emotion regulation).

## Aim and objectives

### Aim

The overall aim of the project is to study feasibility, acceptability and preliminary effects on clinical outcome and target mechanism of an online transdiagnostic emotion regulation treatment called Primary care Online Emotion-regulation treatment (POET).

### Primary objective

Primary objective of this trial is to investigate the feasibility and acceptability of POET relative to an active control treatment.

137 Secondary objective

138 Secondary objectives are to investigate the preliminary effectiveness on clinical  
139 outcomes and target mechanism of POET relative to an active control treatment.

140 Research questions

- 141 1. Are study procedure and design feasible, operationalized as (1) consent rate,  
142 defined as the proportion of eligible participants who consented to inclusion  
143 and randomization; and (2) completion of assessments, defined as completing  
144 at least one clinical outcome immediately post-treatment?
- 145 2. Are POET treatment and the active control treatment acceptable,  
146 operationalized as (1) compliance with the treatments, defined as completing  
147 at least three of six online modules; (2) youth and parent ratings of credibility  
148 and expectancy of treatment after completing the first module; and (3) youth  
149 and parent satisfaction with treatment/course?
- 150 3. Is participation in POET, relative to participation in the active control  
151 treatment, associated with reduction in clinical outcomes, operationalized as  
152 (1) symptoms of anxiety and depression, (2) global functioning, and (3)  
153 symptom severity and improvement, and how large is the effect?
- 154 4. Is participation in POET, relative to participation in the active control  
155 treatment, associated with a reduction in maladaptive emotion regulation  
156 strategies and alexithymia and an increase in adaptive emotion regulation  
157 strategies, and how large is the effect?

158 Time points

159 The primary endpoint of this trial is immediately post-treatment. The secondary  
160 endpoint of this trial is three-month post-treatment.

161 Trial design and procedures

162 Overall trial design

163 This single-blinded, randomized feasibility trial, targeting adolescents with mental  
164 health problems compares POET, an online transdiagnostic emotion regulation  
165 treatment, to an active control treatment. Participants are followed up immediately  
166 post-treatment and three-month post-treatment.

167

168

169

170

## Flow chart

[figure not shown]

## Start and end of the clinical trial

The start of the trial is defined as when the first participant is randomized. The trial ends when the last subject has completed the last three-month post-treatment

## Subject selection

Participants (adolescents and one parent) are recruited through self-referrals and referrals from healthcare professionals. The trial is advertised within Primary care services and on social media.

## Inclusion criteria

- Adolescent between the age of 12 to 17 years
- Presenting with mental health problems
- Having at least one parent willing to participate in the parent course.

## Exclusion criteria

- Severe mental illness that required specialized care or low global functioning corresponding to a Children's Global Assessment Scale (CGAS; )15 score < 41
- Acute suicidality
- Ongoing psychological treatment
- Changes in psychopharmacological medication during the past 2 months
- Insufficient skills in speaking and understanding Swedish
- Life circumstances that could prevent treatment participation (e.g., domestic violence).

## Screening and inclusion

Individuals can access information about the study via a study website or via Primary care services in Stockholm, Sweden. People interested in participating in the study can make a self-referral via the self-assessment tool and website. When potential participants have been referred to the study or have made a self-referral, members of the research project group will contact the parents and give information about the study. If parents and adolescents are interested in participating, they are invited to a digital clinical assessment. Parents and adolescents answer self-assessment measures and sign informed consent before the clinical assessment. Participants between 12 to 14 years old provide verbal consent, while both caregivers, if applicable, provide written consent. Participants between 15 to 17 years old provide written consent themselves. During the assessment interview, the inclusion and exclusion criteria are assessed through clinician-administered interviews and assessments conducted by a licensed psychologist. Hence, eligibility is established before randomization. Individuals who meet the inclusion criteria and no exclusion criteria are offered participation in the study. Excluded participants receive treatment recommendations if needed.

## Withdrawal criteria

Subjects can discontinue their participation in the trial at any time.

## The active treatment

POET will be adapted from online Emotion Regulation Individual Therapy for Adolescents developed by the research group. The main changes will include (1) revisions to make psychoeducation and examples appropriate for youth with mild to moderate mental health problems and less focus on self-harm; (2) reduced treatment length from 12 to 6 weeks; and (3) the inclusion of synchronous video-link meeting. The adaptations are based on prior experience of the target population and qualitative interviews with prior study participants. The theoretical foundation of the POET treatment draws from the Extended Process Model of Emotion Regulation. The youth component of POET will include psychoeducation about emotions and skill training, focusing on five emotion regulation strategies aligned with the emotion-

generative sequence of situation, attention, appraisal, and response. The parent course focuses on how parents can support the adolescent in using more adaptive and fewer maladaptive emotion regulation strategies and skill training in effectively responding to their children's and their own emotions.

#### The active control treatment

The active control will be supportive treatment. This treatment is designed to control for effects of non-specific treatment components that are common to most psychosocial interventions and that are known to be associated with reduction of symptoms, such as receiving general counseling, attention from a therapist, and monitoring of one's emotions and behaviors. The active control treatment is an online Supportive treatment based on an online supportive treatment previously evaluated for social anxiety disorder. It includes psychoeducation on mental health problems and information on five themes related to adolescent well-being (school, family, friends, self-esteem, and social support) Participants are instructed to reflect upon each theme throughout the treatment. None of the active elements of the experimental treatment were included in the active control treatment. The parental course includes weekly reflections on how to support their adolescents' well-being.

#### Therapist support

Throughout treatment, adolescents and parents have regular contact with an assigned therapist through a secure online platform, where the treatment content is also presented. The therapist provides feedback, assists in planning homework assignments, and is available for questions at any time during treatment. The therapists are licensed psychologists with extensive experience in treating adolescents with mental health problems. Therapists will provide both the POET treatment and the active control treatment after careful training in both methods. Therapists will receive weekly supervision.

#### Randomization

Eligible participants will be randomly allocated (1:1) to POET treatment or Supportive treatment. Randomization will be conducted by an independent researcher using a true random number service. The random allocation sequence will be placed in opaque sealed envelopes.

#### Blinding

Assessors are blinded to treatment allocation, and all participants received explicit instructions not to reveal their treatment condition to the blinded assessor. The integrity of the blinding is assessed by having blinded assessors guess the group allocation following each assessment and specify the reason for their guess, choosing between 1) the family accidentally revealed the condition, 2) symptom reduction, 3) global functioning, or 4) a pure guess. Blind assessors are also asked to report whether the group allocation was accidentally disclosed.

## Measures

Outcome measures include both blinded assessor-rated telephone interviews and online self-reported assessments immediately after post-treatment and three-month post-treatment. Data, in the form of clinician- and self-rated assessments, will be collected for all participants pre-treatment, immediately post-treatment, and at three-month post-treatment. An independent rater blind to treatment condition will conduct the immediate post-treatment assessment and the three-month post-treatment assessments.

### *Screening measures*

-Psychiatric comorbidity: This will be clinically assessed with Mini-Kid International Neuropsychiatric Interview, version 6. (MINI KID, ).

-Suicidality: One question that aims to screen for and identify suicidality will be administered weekly to all adolescents.

### *Outcomes for research question 1: (feasibility measures):*

The proportion of eligible participants who consent to inclusion and randomization will be calculated.

The proportion of completed assessments (at least one clinical outcome) immediately post-will be calculated.

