## Power calculations

30 participants will be included in this study, a sufficient number of participants to answer the research questions about feasibility and acceptability. The sample size (N = 30), given an estimate of 20% dropout, gives a power of 80% to detect a meaningful standardized average difference between pre- and post-measurement in each condition of  $d = 0.6$  given alpha level .05.

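### The consent rate counts only families who have already signed consent, so it is either 100% by definition or acceptance among prior consenters, and neither is overall uptake

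*Protocol*

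**What the plan says.** The protocol defines the consent rate twice. Research questions, item 1, has it "defined as the proportion of eligible participants who consented to inclusion", where the consent also covers being randomised. The feasibility measures section repeats it: "The proportion of eligible participants who consent to inclusion and randomization will be calculated". Neither place says more about the denominator or about which act is the consent.

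Screening and inclusion sets the order of events. After a referral or self-referral, the project group contacts the parents and informs them. Then:

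- Only families who say they want to take part get an invitation to an online interview.
- The signature comes next: "Parents and adolescents answer self-assessment measures and sign informed consent before the clinical assessment".
- Eligibility follows: "During the assessment interview, the inclusion and exclusion criteria are assessed through clinician-administered interviews and assessments conducted by a licensed psychologist".
- The offer comes last: "Individuals who meet the inclusion criteria and no exclusion criteria are offered participation in the study".

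The consent rate is one of two outcomes for research question 1, which belongs to the primary objective. Power calculations adds: "30 participants will be included in this study, a sufficient number of participants to answer the research questions about feasibility and acceptability". The protocol states no expected consent rate, target or progression threshold.

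**The concern.** A consent rate in a feasibility trial is normally read as the willingness of suitable families to join once they have been asked. That reading requires eligibility to be known, or at least judged, before the family decides. Here the decision to sign comes first and eligibility is determined afterwards. Families who decline at the information contact, are not interested enough to be invited, or do not sign never have their eligibility determined. They drop out of the numerator and the denominator alike.

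At stake is the answer to half of research question 1. A reader who takes the reported percentage as uptake could plan recruitment for a full trial on too favourable a figure. The sample size of 30 does not help, because the difficulty is who may be counted and not how many are.

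**Working it through.** The protocol gives no consent rate to reproduce, so the check follows the order of steps and then shows the size under assumed values.

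**Order of steps (Screening and inclusion).** Informed → interested and invited → consent signed → assessed → eligibility known → participation offered → randomised. The denominator, eligible families, is formed after the signature. Hence every family in it has signed.

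**Reading A: consent is the signed form.** Rate = (eligible and signed) / (eligible). All eligible families have signed, so the rate is 100% whatever happens in recruitment.

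**Reading B: consent is acceptance of the later offer.** Let q be the share of eligible families who decline that offer. Rate = 1 − q. It can fall below 100%, but it is conditional on an earlier signature.

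**Uptake that also counts early refusers.** Let c be the share of informed families who go on to sign. If eligibility is equally common in signers and non-signers, uptake = c × (1 − q). The ratio of this to the Reading B rate is c, so the stated rate is too high by a factor of 1/c as a measure of uptake.

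The protocol gives neither c nor q. Over an assumed range:

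| q | Rate as defined (Reading B) | Uptake, c = 90% | Uptake, c = 70% | Uptake, c = 50% |
|---|---|---|---|---|
| 0% | 100% | 90% | 70% | 50% |
| 5% | 95% | 85.5% | 66.5% | 47.5% |
| 10% | 90% | 81% | 63% | 45% |
| 20% | 80% | 72% | 56% | 40% |

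The second column does not depend on c.

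**Precision under Reading B.** The number included, 30, is from Power calculations; the numbers of eligible families are assumed. Intervals are exact (Clopper-Pearson).

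| Accepted / eligible | Rate | 95% CI |
|---|---|---|
| 30/30 | 100% | 88.4% to 100% |
| 30/32 | 93.8% | 79.2% to 99.2% |
| 30/34 | 88.2% | 72.5% to 96.7% |
| 30/38 | 78.9% | 62.7% to 90.4% |

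Under Reading B the rate can thus vary appreciably. Under both readings, a refusal before the assessment leaves it unchanged.

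**The case against.** The best defence is that the protocol provides a second decision. Eligible families are offered participation after the interview, and the outcome wording, which names inclusion and randomization, fits acceptance of that offer at least as well as the earlier signature. Willingness to be randomised among families of confirmed eligibility is a useful quantity in a trial with an active control. This stands. A reader might infer that the rate must be close to 100% by construction, but the documents do not support that: it is certain only under Reading A, and nothing in the protocol bounds refusal at the later offer.

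A reader might also infer that a conclusion of feasibility is built in. That is not supported either. No threshold is stated, the protocol says only that the proportion will be calculated, and assessment completion, module completion, credibility and expectancy, and satisfaction also serve the primary objective.

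Nor would dividing by all informed families be a clean replacement. The eligibility of non-signers is never assessed, and recruitment includes self-referral and social media, so that denominator mixes unwilling with ineligible families. The flow chart is not visible in the text reviewed and an analysis plan may exist, so it cannot be said that recruitment counts are absent.

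Finally, the revision history dates the latest change to March 2025, in response to reviewers' comments, and the Statistical analyses section describes some models as already fitted. Replacing the outcome now would be a post hoc change. Naming it accurately and adding counts would not be.

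None of this removes the core point: the denominator is formed after signature, and the term for the numerator is undefined.

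**Conclusion.** The concern holds in this form. The consent rate is conditional on earlier signed consent, and the protocol leaves open which act it counts. It is therefore either uninformative (100%) or a measure of acceptance among families who had already consented. As a statement of overall uptake it is too high by a factor of 1/c: with an assumed c of 90%, 70% or 50%, that is about 1.1, 1.4 or 2 times.

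That size rests on assumed values of c and on equal eligibility in signers and non-signers. If nearly all informed families sign, the overstatement is small. The direction needs only that some eligible families decline before the assessment. The order of steps itself comes straight from the protocol and needs no assumption.

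**What to change.** 1. State which act counts as consent for research question 1: the signature before the assessment, or acceptance of the offer after it.
2. Keep the present measure, taken as acceptance of the offer, but name it *acceptance of inclusion and randomisation among consented, eligible families*, and do not interpret it as overall uptake.
3. Report two further proportions beside it:
   - signed consent among families contacted and informed, leaving out those known to be ineligible at contact, with a note that the eligibility of other non-signers is unknown;
   - eligible among assessed.
4. Give all three with exact 95% confidence intervals, and show refusals at each step.
5. If counts from the contact stage were not kept, say so as a limitation and report only what the later steps allow.

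The cost is a change of wording and the recruitment counts, with no added participants or visits. The project group contacts each referred family, so the counts should be obtainable, although the protocol describes no contact log. The drawback is that the uptake figure will probably be lower than the present rate, and its denominator will include some families of unknown eligibility.
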